### Intervention Group

Participants will receive the standard education provided at the hospital where they give birth. After enrollment, participants in the intervention group will receive messages until 6 weeks post partum. Birthing parents will receive Essential Coaching for Every Mother, and nonbirthing parents will receive Essential Coaching for Every Partner. Figure 1 provides examples of messages from each program. Messages are automatically scheduled according to the infant’s date of birth, beginning on the second evening after birth. Participants who enroll later will receive messages starting from their enrollment date (eg, someone who enrolls on day 5 will not receive messages from days 2-4). TextIt will be used to program and schedule the messages, and Twilio (Twilio Inc) [39] will serve as the secure gateway for sending and receiving messages. Participants are not restricted from seeking additional postpartum support outside of the study. They will continue to have access to standard perinatal care, including mental health services available through primary care providers and community resources.

**Figure 1 figure1:**
[figure not shown]
Essential Coaching for Every Mother (ECEM) and Essential Coaching for Every Partner (ECEP) example SMS text messages.

### Control Group

Participants will receive the standard education provided at the hospital in which they give birth. After enrollment, participants in the control group will not receive any Essential Coaching Postpartum SMS text messages. They are not restricted from seeking additional postpartum support outside of the study. They will continue to have access to standard perinatal care, including mental health services available through primary care providers and community resources. At enrollment, 6 weeks post partum, and 6 months post partum, participants will be sent an SMS text message with a link to complete the follow-up survey.

### Study Measures

Data will be collected from parents using self-reported web-based surveys administered through REDCap [33]. Table 1 outlines the timing of outcome collection. At baseline, demographics will be collected, including age, occupation, marital status, and educational level, as well as newborn information such as birth weight and delivery method. At 6 weeks post partum, a follow-up survey will be conducted to collect data on types of postpartum support sought and received, health concerns, and feeding behavior. All standardized questionnaires listed in Table 1 will be administered at baseline, 6 weeks post partum, and 6 months post partum.

**Table 1 table1:** Timing of measurement and outcome measurement questionnaires.

Outcome domains and variables			Outcome measure		Baseline (enrollment after birth)		After the intervention (6 wk postpartum)		Follow-up (6 mo postpartum)
**Descriptive**									
	Demographics	Parent and infant characteristics^a^		✓					
**Effectiveness**									
	Parenting self-efficacy	Karitane Parenting Confidence Scale [40]		✓		✓		✓	
	Postpartum depression	Edinburgh Postnatal Depression Scale [41]		✓		✓		✓	
	Postpartum anxiety	Postpartum Specific Anxiety Scale [42]		✓		✓		✓	
	Postpartum stress	Postpartum Childcare Stress Checklist [43]		✓		✓		✓	
	General distress	Depression, Anxiety, and Stress Scale [44]		✓		✓		✓	
	Sleep	PROMIS^b^ Short Form Sleep-Related Impairment (4a) and PROMIS Short Form Sleep Disturbances (4a) [45]		✓		✓		✓	
	Coparenting	Brief Coparenting Relationship Scale [46]		✓		✓		✓	
	Relationship satisfaction	Couple Satisfaction Index-4 [47]		✓		✓		✓	
**Implementation**									
	Program satisfaction	Participant satisfaction survey and health service use^a^				✓			

^a^Researcher generated.

^b^PROMIS: Patient-Reported Outcomes Measurement Information System.

### Primary Outcomes

Parenting self-efficacy will be measured using the Karitane Parenting Confidence Scale [40]. This 15-item tool assesses perceived self-efficacy among parents of infants aged birth to 12 months of age and has acceptable internal consistency (Cronbach α=0.81) and test-retest reliability (*r*=0.88) [40]. A cutoff score of 39 or less (out of 45) indicates clinically low perceived parenting self-efficacy [40].

### Secondary Outcomes

Secondary outcomes will be collected using validated self-report measures, as follows:

Postpartum anxiety symptoms will be measured using the Postpartum Specific Anxiety Scale [42], a 51-item valid and reliable tool for assessing anxiety during the first 6 months post partum. A score of 112 or greater indicates clinical levels of anxiety [42].

Postpartum depression symptoms will be measured using the Edinburgh Postnatal Depression Scale [41]. A score greater than 9 (out of 30) suggests possible postpartum depression in both birthing and nonbirthing parents.

Postpartum stress will be measured using the Postpartum Childcare Stress Checklist [43], an 18-item scale assessing parental perceptions of childcare stress in the early postpartum period. Responses are summed to produce a score from 0 to 23, with higher scores indicating a higher level of postpartum childcare stress.

General distress will be measured using the Depression, Anxiety, and Stress Scale [44], a 21-item instrument that assesses the emotional states of depression, anxiety, and stress. Postnatal distress is classified by percentile scores, with total score (between 0 and 63) and a score for the three subscales (between 0 and 21), categorized into 5 severity ranges: normal, mild, moderate, severe and extremely severe, with higher scores indicated greater severity.

Sleep will be measured using the Patient-Reported Outcomes Measurement Information System (PROMIS) Short Form Sleep-Related Impairment (4a) and PROMIS Short Form Sleep Disturbances (4a) [45]. Sleep-related impairment measures perceptions of alertness, sleepiness, and tiredness during usual waking hours, as well as perceived functional impairments during wakefulness associated with sleep problems or impaired alertness. By contrast, sleep disturbance measures perceptions of sleep quality, sleep depth, and restoration associated with sleep. Higher scores indicate greater sleep-related impairment and disturbance.

Relationship satisfaction will be measured using the Couple Satisfaction Index [47], a 4-item scale assessing satisfaction in a relationship. Higher scores indicate greater satisfaction, whereas a score less than 13.5 is associated with notable dissatisfaction.

Coparenting will be measured using the Brief Coparenting Relationship Scale [46], a validated 15-item instrument assessing 5 coparenting dimensions of agreement: closeness, child exposure to conflict, coparenting undermining, endorsement of partner’s parenting, and labor division [46]. Scores range from 0 to 60, with higher scores indicating greater coparenting.

We will also assess the implementation of Essential Coaching Postpartum using output data from the Twilio and TextIt platforms (eg, the number of SMS text messages sent, the number of SMS text messages delivered, error messages, unsubscription rates, and link clicks) as well as open-ended feedback from participants collected at 6 weeks post partum.

### Data Analysis

Data will be analyzed on an intention-to-treat basis. Demographic characteristics, including parental age, marital status, educational level, and delivery method (eg, vaginal or cesarean), will be summarized using means and SDs or percentages, as applicable. Postnatal health care contacts for the parent and infant, health concerns, and feeding behavior will also be reported using means and SDs or percentages, as applicable. Any significant differences in baseline characteristics, assessed using chi-square tests or Mann-Whitney *U* tests, will be adjusted for in subsequent analyses. A *P* value of <.05 will be considered statistically significant for all outcomes.

For the primary and secondary outcomes, analysis of covariance will be used to determine whether scores differ between the 2 groups, with adjustments for pretest scores and any significant baseline characteristics. For the exploratory analysis, dyadic actor-partner interdependence multivariate multilevel modeling will be used to examine each dyad member’s relationship to primary and secondary outcomes after accounting for other explanatory variables. For implementation data, quantitative responses will be reported, and thematic analysis [48] will be conducted to describe participants’ experiences with Essential Coaching Postpartum.

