### Objectives

The primary objective is to compare the effectiveness of Essential Coaching Postpartum with standard care on parenting self-efficacy, mental health (ie, depression, anxiety, and stress), well-being (ie, general distress and sleep), and parenting outcomes (ie, relationship satisfaction and coparenting) among first-time nonbirthing parents in Nova Scotia.

The secondary objective is to compare the effectiveness of Essential Coaching Postpartum with standard care on parenting self-efficacy, mental health, well-being, and parenting outcomes among first-time birthing parents in Nova Scotia.

The explorative objective is to compare the effectiveness of Essential Coaching Postpartum with standard care on parenting self-efficacy, mental health, well-being, and parenting outcomes among first-time parent dyads (ie, both birthing parent and nonbirthing parent) in Nova Scotia.

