### Hypotheses

#### Primary Hypothesis

Our primary hypothesis is as follows: nonbirthing parents who receive Essential Coaching Postpartum will have higher parenting self-efficacy, better mental health (ie, lower scores for depression, anxiety, and stress), greater well-being (ie, lower distress scores and better sleep scores), and higher parenting outcomes (ie, higher relational satisfaction and coparenting) at 6 weeks post partum than those who receive standard care.

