### Sample Size

Sample size calculations were conducted with the assistance of a statistician for both birthing and nonbirthing parents to ensure adequate numbers for each group. As the parent dyad objective is exploratory, no formal calculation was performed for dyads. In the original RCT [25], the baseline parenting self-efficacy score for birthing parents was 35, which is considered clinically low. This value was used for this analysis. On the basis of the SD from the original RCT [25], an improvement of 4 points in the intervention group at 6 weeks is anticipated, which would no longer be classified as clinically low. A total sample size of 141 parents is therefore required, assuming 80% power and a 2-tailed α of .05. As no comparable evidence is available for nonbirthing parents, we will apply the same sample size estimation (n=141) for nonbirthing parents. Allowing for 15% attrition, we plan to recruit a minimum of 166 birthing parents and 166 nonbirthing parents.

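### The primary hypothesis covers nine scores but the primary outcome and sample size cover one, and the P<.05 rule for all outcomes does not say which result decides

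*Protocol article*

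**What the plan says.** The protocol article defines what is primary in two ways.

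- **Broad definition.** The Objectives section says "The primary objective is to compare the effectiveness of Essential Coaching Postpartum with standard care on parenting self-efficacy, mental health", and goes on to well-being and parenting outcomes, in nonbirthing parents. The Objective in the Abstract does the same. The Primary Hypothesis says "nonbirthing parents who receive Essential Coaching Postpartum will have higher parenting self-efficacy, better mental health (ie, lower scores for depression, anxiety, and stress", then adds distress, sleep, relationship satisfaction and coparenting, all at 6 weeks.
- **Narrow definition.** Primary Outcomes contains one measure: "Parenting self-efficacy will be measured using the Karitane Parenting Confidence Scale". Depression, anxiety, stress, distress, sleep, relationship satisfaction and coparenting all appear under Secondary Outcomes. Sample Size also rests on self-efficacy alone: "an improvement of 4 points in the intervention group at 6 weeks is anticipated", and "A total sample size of 141 parents is therefore required, assuming 80% power and a 2-tailed α of .05".

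Data Analysis uses analysis of covariance for primary and secondary outcomes alike and states that a P "value of <.05 will be considered statistically significant for all outcomes". It gives no testing order and does not say what result would confirm the primary hypothesis.

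**The concern.** Eight scores are part of the primary hypothesis and are also secondary outcomes. Both cannot hold in a confirmatory trial, because the label decides which result carries the main claim. With one unadjusted threshold for everything and no success rule, that choice could be made after the results are known. A trial that missed on self-efficacy but reached P<.05 on one sleep form could be reported as supporting its primary hypothesis, and nothing in the article would rule that out.

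This is not a complaint that a multiplicity section is missing. A condensed article may leave that to an analysis plan. An analysis plan could add detail, but it cannot make the Primary Hypothesis and Primary Outcomes sections agree.

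**Working it through.** **Count of scores.** From Primary Hypothesis, Table 1 and Secondary Outcomes: self-efficacy (1), depression (1), anxiety (1), stress (1), general distress as one total (1), sleep as two PROMIS short forms (2), relationship satisfaction (1), coparenting (1). Total 9, of which 8 are labelled secondary.

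**The plan's own figures.** "Allowing for 15% attrition, we plan to recruit a minimum of 166 birthing parents and 166 nonbirthing parents": 141 / (1 − 0.15) = 165.9, rounded up to 166. This reproduces. The 141 cannot be checked independently, because the text says only "On the basis of the SD from the original RCT" and prints no SD. Solving backwards with 70.5 per arm:

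- SD = 4 × √(70.5/2) / (1.960 + 0.842) ≈ 8.48.

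The article states no error rate for the nine scores taken together, so there is no figure to reproduce there.

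**Error rate for the primary hypothesis under each possible reading**, each test two-sided at .05:

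1. *Karitane alone decides.* Error 5%, of which 2.5% is in the favourable direction.
2. *All nine must succeed.* The error cannot exceed that of any single test, so at most 5%. The chance of joint success cannot exceed the chance of success on Karitane, so power is at most 80%. How far below it falls cannot be worked out, because no effect sizes are given for the other eight scores.
3. *Any one suffices.* With independent scores:
   - either direction: 1 − 0.95^9 = 0.370;
   - favourable direction only: 1 − 0.975^9 = 0.204.

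The favourable figure is the one that fits a hypothesis worded in terms of higher self-efficacy, lower symptom scores and so on.

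**Effect of correlation under reading 3.** The article gives no correlations. A simulation of nine test statistics with an assumed common correlation (1,000,000 draws) gives:

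| Assumed correlation | Either direction | Favourable only |
|---|---|---|
| 0 | 37.0% | 20.4% |
| 0.3 | 32.6% | 16.4% |
| 0.5 | 27.0% | 13.5% |
| 0.7 | 20.3% | 10.2% |

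**What reading 3 would cost if controlled.** Bonferroni gives 0.05/9 = 0.0056 per test, with a two-sided critical value of about 2.77. At 141 evaluable, the expected test statistic for the 4-point difference is 1.960 + 0.842 = 2.80, so power is Φ(2.80 − 2.77) ≈ 51% instead of 80%. Restoring 80% would need about 236 evaluable parents, or 236/0.85 ≈ 278 recruited, per parent type, using the implied SD of 8.48.

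**The case against.** The strongest reply is that the primary outcome can be identified. Primary Outcomes names one scale, Sample Size uses the same scale at 6 weeks, and everything else is headed secondary. The P<.05 sentence sets a significance level per outcome, not a success rule for the hypothesis. The hypothesis also joins its outcomes with *and*, which read literally requires all of them. On either of those readings the error is at most 5%. This stands, and it limits the point: inflation follows only if one success among nine is allowed, and no section says that it is.

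Three stronger conclusions that a reader might draw do not hold.

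- *The trial can claim success by chance 20–37% of the time.* That range counts significant differences in either direction, while the hypothesis is directional. It assumes the any-one rule, and its lower end assumes a correlation of about 0.7 that the article does not give.
- *With the three distress subscales there are twelve scores and a 46% error rate (1 − 0.95^12).* The distress total runs from 0 to 63 and each subscale from 0 to 21 (3 × 21 = 63), so the total cannot be treated as independent of its subscales. Nor does the article say the subscales will be tested separately.
- *There are 36 tests (9 scores × 2 parent types × 2 time points), so 1.8 false positives are expected (36 × 0.05).* The sum is right, but the birthing-parent and 6-month results are labelled secondary hypotheses and say nothing about error on the primary one.

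The reply does not remove the contradiction. If Karitane alone decides, the objective and primary hypothesis are worded wrongly. If all nine must succeed, the Primary Outcomes heading and the stated power do not match the hypothesis. If any one suffices, error is uncontrolled. Every reading requires a change to the text.

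**Conclusion.** Wrong as written. The objective and primary hypothesis name nine scores, the primary outcome and sample size name one, and the significance sentence covers all outcomes without saying which result decides.

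The consequence depends on which reading governs. The article best supports Karitane alone, which keeps the error at 5% and the stated power intact. Requiring all nine also keeps the error at most 5%, but the 80% power does not apply. The any-one reading, neither stated nor excluded, would raise the false-positive rate to at most 37% in either direction or 20% in the favourable direction under independence, and to less under positive correlation.

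The count of nine assumes that distress is tested as one total and sleep as two scores. The firm finding is the unresolved definition of success; the percentages are conditional on a rule that the article does not state.

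**What to change.** - Reword the Abstract objective, the Objectives section and the Primary Hypothesis so that the single confirmatory test is the Karitane score at 6 weeks in nonbirthing parents, two-sided .05. This matches Primary Outcomes and Sample Size.
- Qualify the sentence on all outcomes in Data Analysis: the other scores, the 6-month results and the birthing-parent results are secondary and cannot by themselves confirm the primary hypothesis. Either report them as adjusted differences with 95% confidence intervals, or test them under a multiplicity procedure that the sponsor chooses and states. The contradiction does not dictate a particular hierarchy or adjustment.

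The cost is small. The 141 evaluable and 166 recruited per parent type, and the power for self-efficacy, are unchanged. The downside is that fewer scores can support the primary claim. The article reports 5 nonbirthing parents enrolled by September 15, 2025, so the wording could be settled before much outcome data accrue.

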### Randomization

Participants will be randomly assigned in a 1:1 ratio to either the intervention or control group using the TextIt platform’s “split randomly” function. This function distributes contacts equally across pathways, ensuring allocation to either the intervention or control condition. Randomization will occur only after a participant has given birth.

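### ANCOVA covariates beyond the pretest score are picked by testing baseline differences between arms, so the primary model depends on observed imbalance and not on prognosis

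*Protocol article*

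**What the plan says.** The Data Analysis section gives the rule twice. First in general: "Any significant differences in baseline characteristics, assessed using chi-square tests or Mann-Whitney" U tests "will be adjusted for in subsequent analyses". Then for the ANCOVA of the primary and secondary outcomes, which is run "with adjustments for pretest scores and any significant baseline characteristics".

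The candidates are not a closed set. Data Analysis gives four examples ("Demographic characteristics, including parental age, marital status, educational level, and delivery method"). Study Measures adds occupation and birth weight, which makes six named across the two sections, again as an open list.

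The only threshold in the section is a P "value of <.05 will be considered statistically significant for all outcomes". That it also governs the baseline tests is my inference.

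Randomization describes a simple split: "Participants will be randomly assigned in a 1:1 ratio", with no stratification mentioned.

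**The concern.** A between-arm P value measures imbalance. It carries no information on whether the variable predicts parenting self-efficacy. Selecting on it has three consequences:

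- Variables with no prognostic value can enter the model through an accident of allocation.
- Variables that do predict the outcome stay out whenever they happen to balance, although adjusting for them would sharpen the comparison.
- The form of the primary model is settled only once baseline data are in. Because the candidate list is open, even the set of tests is not fixed. The nonbirthing-parent analysis (primary objective) and the birthing-parent analysis (secondary objective) can end up with different covariates for no substantive reason.

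At stake are the pre-specification of the primary analysis and some precision. The rule is written out in the article, so it is not a detail left to an analysis plan that we cannot see.

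**Working it through.** **Inputs from the article (Sample Size).** "assuming 80% power and a 2-tailed α of .05"; "an improvement of 4 points in the intervention group at 6 weeks is anticipated"; 141 analysed per parent type; 15% attrition. The SD comes from the earlier trial and is not stated.

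**The plan's own figures.** 141 / (1 − 0.15) = 165.9, so 166 reproduces. The 141 cannot be checked without the SD. If it came from an unadjusted two-sample comparison (an assumption), the implied SD is 4 / [(1.960 + 0.842) × √(2/70.5)] = 8.48. The power figures below use an assumed SD of 8.42 or 8.48, which are practically the same.

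**How often chance alters the model.** For k independent tests at P<.05 with no true difference, P(at least one added) = 1 − 0.95^k:

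- k = 4: 18.5%
- k = 6: 26.5%
- k = 8: 33.7%
- k = 10: 40.1%

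If two candidates are truly prognostic, the chance that the rule picks neither is 0.95² = 90%. Simulation with 6 candidates agrees: 25–27% of trials departed from the pretest-only model, and about 90% contained neither prognostic covariate.

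**Power forgone, by formula.** Assume SD 8.42, pretest correlation 0.5, and two independent prognostic covariates each correlated r with the outcome. Residual SD = 8.42 × √(1 − 0.25 − 2r²); SE = residual SD × √(2/70.5); power = Φ(4/SE − 1.96).

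| Covariates in the model | Residual SD | SE | 4/SE − 1.96 | Power |
|---|---|---|---|---|
| Pretest only | 7.292 | 1.228 | 1.297 | 90.3% |
| Plus two, r = 0.1 | 7.194 | 1.212 | 1.341 | 91.0% |
| Plus two, r = 0.2 | 6.892 | 1.161 | 1.486 | 93.1% |
| Plus two, r = 0.3 | 6.357 | 1.071 | 1.776 | 96.2% |

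Fixed covariates therefore gain about 1, 3 and 6 points over the pretest-only model.

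**Power forgone, by simulation of the rule itself.** Under the same assumptions, with six candidates of which two are prognostic, the rule gives about 89–90% power. Fixed covariates give 89%, 92% and 95% for r = 0.1, 0.2 and 0.3. The difference is roughly 0 to 6 points.

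A second simulation (SD 8.48; 4,000 trials per scenario; Monte Carlo error about 0.6 point per figure) varied the pretest correlation and the share of outcome variance that the two covariates explain:

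| Pretest correlation | Variance explained | Pretest only | Article's rule | Fixed covariates |
|---|---|---|---|---|
| 0.3 | 5% | 83.1% | 82.6% | 84.4% |
| 0.3 | 10% | 83.0% | 83.3% | 87.4% |
| 0.3 | 20% | 82.6% | 83.2% | 90.2% |
| 0.5 | 5% | 89.8% | 89.8% | 91.2% |
| 0.5 | 10% | 89.1% | 89.4% | 92.5% |
| 0.5 | 20% | 89.3% | 90.1% | 96.1% |

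The rule performs about as well as pretest-only ANCOVA. Its shortfall against fixed covariates runs from 1.4 to 7 points here, the largest being with the weaker pretest and the strongest covariates.

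**Type I error.** With no true effect, the rule rejected in 4.3–5.1% of trials in the first simulation and 4.1–5.5% in the second.

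**The case against.** The best defence is that little is lost. The pretest score, probably the strongest predictor, is always in the model. The rule is stated in advance and looks at baseline data, not outcomes. The size of any gain from fixed covariates rests on prognostic strengths that the article does not give, and with weak covariates it is close to nil. All of this stands, and it limits the point to model specification and a possible gain in precision.

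A second defence is that imbalance here need not be pure chance. Under Screening and Baseline, allocation precedes consent and the baseline survey, and dyads split across arms are both moved to the intervention. Under Blinding, participants know their arm. Under Eligibility Criteria, those who do not complete the baseline survey are withdrawn. Some baseline differences could therefore be systematic, and the 19% and 26% figures describe the chance component only. This is a reason to examine imbalance. It does not make a significance screen at about 141 parents a good safeguard, because the screen can miss a systematic difference in a strong predictor and react to a trivial one in an irrelevant variable.

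Three stronger readings are tempting, and the documents do not support them:

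- *A reader might infer false-positive inflation.* The simulated type I error is near nominal.
- *A reader might infer that the trial is underpowered.* At the stated 4-point effect the rule matches pretest-only ANCOVA, which on the unadjusted sample-size assumption is at or above 80%.
- *A reader might infer that the nonbirthing and birthing effects become non-comparable.* They belong to separate objectives and no comparison between them is planned. In a linear ANCOVA under randomisation the target effect is also the same whichever baseline covariates are used; what changes is the model and its precision.

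**Conclusion.** The point holds as a defect of specification. Covariates beyond the pretest score are selected on imbalance, from an open list, so the primary model is not fixed in advance and will usually omit prognostic variables. That conclusion needs no numerical assumption.

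The frequency of chance additions (about 19% with 4 candidates, 26% with 6) assumes independent tests at P<.05 and chance imbalance only. The forgone power, roughly 0 to 6 points at the 4-point effect, is conditional on an SD of about 8.4, a pretest correlation of 0.5 and two covariates correlated 0.1 to 0.3 with the outcome. It can reach 7 points with a pretest correlation of 0.3 and covariates explaining 20% of the variance. It is a gain not taken, measured against a better model, and it is not a shortfall from the planned 80%. The change is worth making because it is nearly free, but the validity of the trial does not hang on it.

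**What to change.** - Delete baseline significance testing as a way of choosing covariates, and describe baseline by arm without P values.
- Fix the ANCOVA covariates now: the baseline score of the outcome plus a short list chosen on prognostic grounds from characteristics that are settled before randomisation and already collected. Parental age and educational level are examples; the coding of education should be stated. The article gives no evidence on which variables predict the outcome, so the sponsor should supply the rationale.
- If delivery method is used, restrict it to the birthing-parent model. Eligibility Criteria admits nonbirthing parents by adoption or surrogacy, for whom it may be unknown or irrelevant.
- Do not adjust for enrolment as a dyad. The partner is contacted after randomisation and split dyads go only to the intervention, so dyad status can be affected by allocation.
- Keep adjustment for observed imbalance, including any arising from consent after randomisation or from dyad reassignment, as a labelled sensitivity analysis.

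The cost is a sentence or two in the protocol and analysis plan, no new data, and a few degrees of freedom out of about 140 (more if education is coded in several categories). The timing is favourable: Results reports only 11 birthing and 5 nonbirthing parents enrolled by September 15, 2025.
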